**Methods/design:**

This is a single-blind, multicentre, randomized controlled trial. At least ninety-three community-dwelling older adults with MCI aged 60 or above will be recruited. They will be randomly allocated into four groups: Physical Training alone (PT), Cognitive Training alone (CT), combined Physical And Cognitive Training (PACT) and Waitlist Group (WG). The PT group will perform exercises (flexibility, endurance, strengthening, and balance training) for 60–90 min three times per week for 12 weeks. The CT group will be involved in a paper-based training focusing on orientation, memory, attention and executive functioning for 60–90 min per session, once a week for 12 weeks. The PACT group will undergo cognitive training incorporated in physical exercise for 60–90 min three times per week for 12 weeks. The WG will receive the intervention, combined physical and cognitive training, at a later date. Assessors blinded to participant allocation will conduct pre-intervention, post-intervention, and 6-month follow-up assessments. The primary outcome measure will be falls rate. The secondary outcome measures will be Physiologic Profile Assessment and Falls Risk for Older Persons in the Community, and assessments that evaluate cognitive, physical and psychological factors related to falls.

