### Sample size computation

The sample size and power calculations will be based on fall rate which is the primary outcome of the study. Using statistical software Gpower 3.1.9.2, a priori power analysis was conducted using the computed effect size (Cohen’s d = .39) from Trombetti et al. (2011) [46]. Assuming 80% power with 5% Type 1 error and four groups, the calculated total sample size is 80. Considering a 16% dropout rate (Trombetti et al., 2011) [46], the total number of participants is inflated to 93. There should be at least 23 participants per group.

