## Discussion

The objective of this proposed study is to determine the effectiveness of combined physical and cognitive training on preventing falls and reducing the risk of falls among community-dwelling older adults with MCI. To our knowledge, this is the first trial that will investigate the direct effect of combined physical exercise and cognitive training on falls in this target population [73].

A fall could result in fatal or non-fatal physical injuries [53, 74], psychosocial problems [75], and also brings about economic burden to the family and community [76–78]. Older people with MCI are at a heightened risk for falls [1]. It is essential, therefore, to scientifically determine which treatment programs are most effective in this population [79].

A previous study reported that all aspects of balance control deteriorate with increasing severity of cognitive impairment and that executive function plays an important role in balance control [80]. Early intervention, therefore, is vital for the care of older people with MCI to prevent or retard its progression to dementia and to prevent the occurrence of falls [2, 26]. This study will contribute knowledge on the impact of proactive measures in older persons with MCI.

We are anticipating that since the training programs will run for 12 weeks, we might have difficulty recruiting participants and also sustaining their attendance throughout the intervention period. To address this, the researchers will be working closely together with the local OSCA coordinators in inviting participants and following them up. Travel allowance and refreshments will also be provided to the participants every time they attend a session to encourage them to be diligent in their involvement. Participants may also drop-out due to various reasons (busy schedule, relocation, low motivation, diseases) which is why the sample size was inflated by 16% [46].

In summary, this trial will provide insight into the effect of integrating cognitive training into physical exercise in preventing falls and reducing physical, cognitive and psychologic risks of falls in older persons with MCI living in the community. Healthcare professionals and practitioners in the geriatric field will be provided with validated community-based interventions whose effect on falls and fall-related risk factors is scientifically evaluated.

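### The 16% dropout allowance is applied by multiplying (80 × 1.16 = 93) rather than dividing (80 / 0.84 = 95.2), so 93 recruits leave about 78 completers, not 80

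*Protocol article*

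**What the plan says.** Under Sample size computation, the protocol article states that "the calculated total sample size is 80", for 80% power, 5% type 1 error and four groups. It then makes an allowance for attrition: "Considering a 16% dropout rate", taken from an earlier trial, after which "the total number of participants is inflated to 93. There should be at least 23 participants per group". The second sentence of that quote sets a floor for each arm.

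The Abstract (Methods/design) carries the result forward as the recruitment minimum: "At least ninety-three community-dwelling older adults with MCI aged 60 or above will be recruited". The Discussion lists reasons why participants may leave and presents the inflation as the protection against this: "which is why the sample size was inflated by 16% [46". No section gives a larger target.

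**The concern.** An inflation for dropout should make the number who remain equal the number that the power calculation asked for. If a fraction d of those enrolled is lost, enrolment must be n / (1 − d). Multiplying by (1 + d) is a common slip. It adds 16% of the 80 who are meant to remain, whereas the loss is 16% of the larger number enrolled, so the result is always too small.

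What is at stake is whether the stated recruitment minimum does what the article says it does. The Discussion expects difficulty in recruiting and in sustaining attendance over 12 weeks, and it relies on this allowance as the answer to dropout.

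**Working it through.** **Inputs, all from the protocol article**
- Calculated total before dropout: 80, or 20 in each of four groups (Sample size computation)
- Dropout: 16% (Sample size computation; Discussion)
- Total after inflation: 93 (Sample size computation; Abstract)
- Minimum per group: 23 (Sample size computation)

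**Step 1. Reproduce the plan's figure.** Multiplying, n × (1 + d) = 80 × 1.16 = 92.8, which rounds up to 93. This matches exactly, and the Discussion's description of the inflation agrees with it. Dividing does not give 93.

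**Step 2. Inflate so that 80 remain.** n / (1 − d) = 80 / 0.84 = 95.24, rounded up to 96. Per group, 20 / 0.84 = 23.8, rounded up to 24, and 4 × 24 = 96. Check: 96 × 0.84 = 80.6.

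**Step 3. What 93 delivers at 16% dropout.** 93 × 0.84 = 78.1, or 78.1 / 4 = 19.5 per group against 20. The gap is 80 − 78.1 = 1.9 completers.

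**Step 4. The dropout that 93 can absorb.** 1 − 80/93 = 0.140. The stated total covers dropout of up to 14.0%, not 16%.

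**Step 5. Chance of reaching 80 completers.** If each participant completes independently with probability 0.84 (an assumption), the probability of at least 80 completers is 0.36 with 93 enrolled and 0.64 with 96.

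**Step 6. Effect on power.** The article does not name the test family. If 0.39 was entered as Cohen's f in a four-group one-way ANOVA at the 5% level (an assumption, since the article labels it Cohen's d), power is:

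| Total analysed | Power |
|---|---|
| 80 | 0.825 |
| 78 | 0.814 |
| 76 | 0.802 |

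On that reading, losing two completers costs about one percentage point of power and leaves it above 80%.

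**Step 7. Total against per-group minimum.** 93 / 4 = 23.25. Groups of 23, 23, 23 and 24 add to 93, and each has at least 23.

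**The case against.** The strongest reply is that the slip has little practical effect. Both 93 and 23 are stated as minimums, so recruiting more could close the gap. The Statistical analysis section specifies intention-to-treat for dropouts and computes fall rate over the time each participant was monitored. Someone who leaves early may therefore still contribute follow-up to the primary outcome, and counting every dropout as a total loss overstates the damage. On the one reading of the power calculation that comes near 80, 78 participants still give more than 80% power. All of this stands as an argument about size. It does not make the inflation correct: the article chose to allow for 16% dropout, and a stated minimum should suffice under its own assumption.

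It can also be said that the article does not define the denominator of the 16%. If dropouts were counted per completer, 93 would be right. That is not the usual meaning of a dropout rate, and nothing in the article suggests it. It would correspond to 0.16 / 1.16 = 13.8% of those enrolled.

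Two stronger readings are tempting and not supported. First, a reader might multiply 4 × 23 = 92 and infer that the per-group and total figures contradict each other. They do not: 23 is a floor for each arm, Step 7 shows that both statements can hold together, and no section permits a total of 92. Second, a reader might infer that the slip leaves the trial underpowered. Step 6 gives no support for that. How 80 follows from 0.39 is a separate question. The ANOVA in Step 6 needs only about 76 for 80% power, so it does not reproduce 80 exactly. The point here takes the plan's 80 as given.

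**Conclusion.** The point holds as an arithmetic error with a small effect. The stated total of 93 does not preserve the calculated 80 at the stated 16% dropout: it leaves about 78, and it would keep 80 only with dropout of 14.0% or less. The enrolment consistent with the plan's own inputs is 96, three more than stated.

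The conclusion rests on reading 16% as a share of those enrolled and on taking 80 as the number meant to remain. The statement that power is barely affected rests on the further assumption that 0.39 was used as f in a four-group ANOVA. Neither an inconsistency between 93 and 23 per group nor a material loss of power is established.

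**What to change.** Correct the inflation sentence under Sample size computation in one of these ways:
- **Keep 93 and the 16% rate:** state that 93 recruited leaves about 78 after 16% dropout.
- **Keep 93 and the 80:** state that 93 keeps 80 provided dropout is at most 14%.
- **Keep both the 16% rate and the 80:** change the total to 96 and the per-group minimum to 24, and change the minimum in the Abstract to match.

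In each case, align the Discussion sentence on the dropout allowance with the option chosen. Under the first two, the Abstract's minimum of 93 and the floor of 23 per group can stay as they are.

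The first two options cost only a text edit and remain available if recruitment has closed (the Appendix timeline places it in June–September 2017). The third costs three additional participants.

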### Interventions

#### Physical training alone (PT)

The participants in the PT group will be performing a series of physical exercises as a group supervised by trained physiotherapists. To ensure proper guidance and safety in the performance of the exercises, there will be one physiotherapist for every five participants.

The exercise program will start with 5–10 min of warm-up including calisthenics and general flexibility exercises, followed by 60–90 min of multicomponent exercise programme including endurance, strength and balance exercises (with a focus on balance training), and will end with 5–10 min of cool down including calisthenics and general flexibility exercises. This will be done three times per week over 12 weeks to achieve the recommended minimum accumulated 40 h of exercise [13]. The exercises will be progressed individually, increasing the repetitions or sets first before the resistance, to maintain a moderate level of exercise intensity which is 5 to 6 on a scale of 0 to10 for the level of physical exertion [47]. Rest periods will be provided whenever necessary. Table 1 shows the types of exercises included in this program.

**Table 1 Tab1:** Physical training program

Periods	Exercises	Progression
Warm-up (5–10 min)	Calisthenics and general flexibility	
Multicomponent exercise programme (60–90 min)	Walking over 10 m 1. Walking forward-backward, sideways 2. Turning figure of 8 walking 3. Tandem walking	10–12 rounds; 1–3 sets Increase step length and speed Over obstacles
	Sit-to-stand	8–12 repetitions; 1–3 sets Lower chair height
	Heel and toe raises	8–12 repetitions; 1–3 sets Hold or raise for longer
	Stepping in different directions	8–12 repetitions; 1–3 sets Longer or faster steps Step over obstacle
	Step-ups 1. Forward 2. 2. Lateral	8–12 repetitions; 1–3 sets Increase step height
	Graded reaching in standing 1. Table top - side to side, forward and diagonal reaching 2. Tapping markers on the wall 3. 3. Reaching down to chair, stool or floor	8–12 repetitions; 1–3 sets Narrower foot placement Increase distance to reach Standing on a softer surface (rubber mat) Stepping while reaching
Cool-down (5–10 min)	Calisthenics and general flexibility	

The exercises were based on the recommendations of Sherrington and Tiedemann (2015) [48] and were selected because of the minimal use of sophisticated equipment which is important in an exercise regimen designed for a community setting. The participants will be given brochures containing simplified exercise instructions with illustrations and printed using a large font size to help them remember the exercise routines and encourage them to perform the exercises at home.

#### Cognitive training alone (CT)

The participants in the CT group will be involved in a set of paper-based cognitive exercises as a group supervised by trained occupational therapists. To provide close monitoring and immediate feedback during the training, there will be one occupational therapist for every five participants.

The intervention will start with 5–10 min of warm up to give the instructions, followed by 60–90 min of cognitive training designed to train specific cognitive functions such as orientation, memory, attention and executive function, with emphasis on executive function which is associated with increased risk for falls in older adults [25], and will end with 5–10 min of cool down for feedback and processing of responses. This will be done once a week for 12 weeks which is the optimal duration of cognitive training [30]. Even though the cognitive training is delivered in a group, the difficulty level and progression will be individualized. Rest periods will be provided whenever necessary.

Table 2 shows the contents of the cognitive training. The contents of training for orientation and attention were based from Brum et al. (2009) [49], and Vojtkofsky and Feldman (2015) [50]. For memory, training will include rehearsal, association, visual imagery and concentration. The use of multiple strategies in memory training is chosen as larger improvement is expected with this approach compared to single strategy approaches [50, 51]. For executive function, training will consist of extensive repeated practice of practical tasks to simulate usual daily activities instead of relying on strategies to strengthen cognitive processes. This is founded on the process-based approach which has been proven to be highly effective in improving executive function [27].

**Table 2 Tab2:** Cognitive Training program

Periods	Components	Content
Warm-up (5–10 min)	Giving of instructions	
Cognitive training (60–90 min)	Orientation training	Orientation to person, place, and time with or without external cues like newspaper, calendar a. person – give full name, relatives, neighbors, age, occupation; name public officials b. place – provide address, location of islands/cities/provinces, favorite place/destination c. time – determine current time, day, month and year; schedule of TV shows; special occasions; weather, season
	Memory training	*Rehearsal* • verbally repeating a series of numbers or letters *Association* • face-name recognition – associating person’s name with facial or behavioral characteristics *Visual imagery* • having mental representation of a set of animals, fruits, or common objects and combinations *Concentration* • play card game to turn over 3–6 pairs of matching cards
	Attention training	*Auditory attention* a. Clapping, tapping or stamping upon hearing specific words b. Coloring a picture or folding a paper following dictation c. Identifying the title or artist of a song being played *Visual attention* a. Counting the number of animals seen in a picture b. Encircling specified words in a paragraph/ word hunt c. Completing a trace maze
	Executive function training	From a mixed set of objects on a table, a. Group the items into three and set aside objects which do not belong to any group. b. Arrange items following a model (e.g. table setting, smallest to largest, alternating pattern) Copying a drawing (pyramid, cylinder, house); dot copy Computation of allowance, expenses, change
Cool-down (5–10 min)	Feedback and processing of responses	

The paper-and-pencil format of cognitive training is selected in consideration of the low economic situation of the community. The participants will be given educational brochures with large fonts and illustrations to inform them about the importance of maintaining or improving their cognitive abilities citing specific ways to be mentally active in old age.

#### Physical and cognitive training (PACT)

The participants in the PACT group will be performing activities that integrate cognitive training in physical exercise routines as a group supervised by trained personnel either physiotherapists or occupational therapists. To ensure proper guidance, safety, close monitoring and immediate feedback about their performance of the activities, every five participants will be supervised by one therapist.

The PACT programme will start with 5–10 min of warm-up including calisthenics and general flexibility exercises, followed by 60–90 min of exercises similar in design, intensity and progression with the PT group but with cognitive components incorporated in each type of exercise, and will end with 5–10 min of cool down including calisthenics and general flexibility exercises and a post-session discussion to recall the activities performed in the just-concluded session. This will also be done three times per week over 12 weeks. Rest periods will be provided whenever necessary. Table 3 presents the design of the PACT program. The participants will likewise be given the same brochures given to the PT and CT groups for additional information and reference.

**Table 3 Tab3:** Physical and cognitive training program

Periods	Exercises	Progression
Warm-up (5–10 min)	Calisthenics and general flexibility	
Multicomponent exercise programme (60–90 min)	Walking with executive function training • From a mixed set of objects (30 pieces) on a table at the start of the line, bring one object at a time walking over 10 m towards another table to sort the objects properly in 3–4 separate groups. Walking is done forward, backward, sideward, in figure of 8, or tandem.	10–12 rounds; 1–3 sets Increase step length and speed Walking over obstacles
	Sit-to-stand with orientation training • Stand every time to answer questions about orientation to person, place and time	8–12 repetitions; 1–3 sets Lower chair height
	Heel and toe raises with attention training • Follow visual cues to do heel or toe raises	8–12 repetitions; 1–3 sets Hold or raise for longer
	Stepping in different directions with memory training • Stepping on a set of specified number and sequence of markers on the floor	8–12 repetitions; 1–3 sets Longer or faster steps
	Step-ups with attention training • Follow verbal instructions on which foot to use to step-up	8–12 repetitions; 1–3 sets Increase step height
	Graded reaching in standing with executive function training a. Table setting activity (arrange plates, utensils, glasses based on picture model) b. Arranging objects from smallest to largest, or in alternating pattern c. Copying a drawing (pyramid, cylinder, house); dot copy d. Computation of allowance, expenses, change	8–12 repetitions; 1–3 sets Narrower foot placement Increase distance to reach Standing on a softer surface (rubber mat) Stepping while reaching
Cool-down (5–10 min)	Calisthenics and general flexibility With memory training (summarize what activities were accomplished after the session in correct sequence and details)	

#### Waitlist group (WG)

The participants in the WG will serve as the control group on waitlist. They will be instructed to go on with their usual daily routine and will receive the intervention, combined physical and cognitive training, at a later date.

### Outcomes measures

The following primary and secondary outcome measures will be performed by trained assessors blinded to the group allocation. Measurements will be taken at baseline, at the conclusion of the intervention period, and 6 months post-intervention. Additional information regarding the exercise behavior and the physical and social activities participated in by the eligible participants in the last 6 months will be obtained during the 6 months post-intervention follow-up assessments [52].

### Primary outcome measure

#### Falls rate

Each participant will be given a calendar diary to mark any incidence of fall on a weekly basis during the assessment period. A relative or caretaker of the older person will be asked to validate the information. The confirmation by another person is done because self-reporting techniques, particularly for individuals with cognitive impairment, may not be accurate due to recall bias [53]. Monthly phone calls will be done to update the falls history of each participant.

### Secondary outcome measures

The secondary measures will be assessments that evaluate overall fall risk, cognitive, physical and psychological factors related to falls.

#### Overall fall risk

The overall fall risk will be determined using the short-form Physiological Profile Assessment (PPA) and the Falls Risks for Older People in the Community (FROP-Com) Screen.

The PPA short form is a valid, reliable and objective series of tests used to evaluate the physiologic risks of falls and to classify fallers from non-fallers [54]. It is composed of five subtests on 1) visual contrast sensitivity, 2) proprioception, 3) hand reaction time, 4) knee extensor muscle strength, and 5) postural sway [55]. Data from these tests will be encoded in a web-based software program such that the performance of one participant is compared to a normative database to determine whether the individual has a low or high risk of falls [55].

The FROP-Com Screen is a brief screening tool used to determine older persons who are prone to fall [56]. It is composed of three items on 1) the number of incurred falls within the past 12 months, 2) the level of dependence in doing instrumental ADLs, and 3) balance in walking and turning of older adults [56]. A score of 0–3 means the older adult has a low risk for falls, while a score from 4 to 9 denotes a high risk for falls [56].

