## Appendix

**Table 4 Tab4:** Timeline of the study

Research Highlights	Actual/Expected dates of implementation
Participant recruitment	June–September 2017
Baseline assessment	August–September 2017
Randomization	September 2017
Post-treatment assessment	December 2017–January 2018
9mons post baseline assessment	June–July 2018
Study completion	August 2018

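### The 12-month falls item in FROP-Com blunts it as a follow-up outcome: about 75% of its window precedes the intervention at the post-intervention visit, and about 25% at the last visit

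*Protocol article*

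**What the plan says.** The protocol article's abstract (Methods/design) gives FROP-Com outcome status: "The secondary outcome measures will be Physiologic Profile Assessment and Falls Risk for Older Persons in the Community". Under Secondary outcome measures, Overall fall risk, it is one of two instruments for that construct; the other is the short-form PPA. The same section describes its purpose: "The FROP-Com Screen is a brief screening tool used to determine older persons who are prone to fall". The first of its three items is "the number of incurred falls within the past 12 months". The other two items cover dependence in instrumental ADL and balance when walking and turning. Totals of 0–3 are classed as low risk and 4–9 as high risk.

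Outcomes measures sets the visits for all primary and secondary measures: "Measurements will be taken at baseline, at the conclusion of the intervention period, and 6 months post-intervention". The programmes last 12 weeks (PT: "This will be done three times per week over 12 weeks"; CT: "This will be done once a week for 12 weeks"; PACT has the same length). Table 4 in the Appendix labels the last visit "9mons post baseline assessment", which agrees with 12 weeks plus 6 months.

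Nothing in the article shortens the falls window at follow-up, drops that item, or limits FROP-Com to baseline. Falls during the study are collected separately by calendar diary, validation by a relative or caretaker, and monthly calls (Primary outcome measure, Falls rate). The article does not say that these records are used to score the FROP-Com item.

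**The concern.** An outcome meant to show a change produced by treatment should observe mainly time under or after treatment. Here the first follow-up comes about 3 months after the start, while the falls item looks back 12. The item then consists largely of the same months that were scored at baseline, yet Statistical analysis tests pre- to post-intervention change.

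Reducing the risk of falls is part of the stated aim and hypothesis, and FROP-Com is one of only two measures of overall fall risk. If its post-intervention result shows no difference, that could reflect the look-back window and not the programmes. If its last-visit result does show a difference, part of it may repeat the falls-rate result and not add to it.

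The instrument, window and visits are all fixed in the text, so this is not a detail left to a fuller document.

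**Working it through.** The plan gives no figure of its own to reproduce on this point. The check is arithmetic on the window.

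**Inputs**
- Look-back of the falls item: 12 months (Overall fall risk).
- Intervention length: 12 weeks, about 3 months (the three programme descriptions).
- Last visit: 6 months after the intervention, 9 months after baseline (Outcomes measures; Table 4).
- Assumed, not in the documents: a constant fall rate, and a reduction *r* that acts fully from the first day.

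**Share of the window before the intervention** = 1 − (time since start ÷ window length)

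| Visit | In months | In weeks |
|---|---|---|
| Post-intervention | 1 − 3/12 = 75% | 1 − 12/52 = 76.9% |
| 6 months later | 1 − 9/12 = 25% | 1 − 38/52 = 26.9% |

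**Sensitivity to the calendar in Table 4.** Baseline is August–September 2017 and the post-treatment visit is December 2017–January 2018. The extreme pairings of dates give 62 to 183 days, so the pre-baseline share runs from 1 − 62/365 = 83% to 1 − 183/365 = 50%. These are outer bounds, since 62 days is shorter than the 84 days of a 12-week programme. For the last visit (June–July 2018) the extremes are 244 and 364 days, giving 33% and 0.3%. At the post-intervention visit, therefore, half the window or more is pre-baseline on any pairing.

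**Overlap with the baseline score.** With the start of intervention at month 0, the baseline window runs from −12 to 0 and the post-intervention window from −9 to +3. They share 9 months. A person's change in count is the falls in months 0 to +3 minus the falls in months −12 to −9; the shared months cancel. At the last visit the window runs from −3 to +9. It shares 3 months with baseline, and its other 9 months are the trial period itself.

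**Illustration of the attenuation.** At a constant rate, apparent reduction in the 12-month count = *r* × on-study share.
- Post-intervention, *r* = 40%: 0.25 × 40% = 10%.
- Last visit, *r* = 40%: 0.75 × 40% = 30%.
- Over the outer calendar bounds at the post-intervention visit: 62/365 × 40% = 6.8% to 183/365 × 40% = 20.1%.

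The 40% is an assumption. The relation is proportional, so for any *r* the count shows one quarter of the true reduction at the first follow-up and three quarters at the last. These figures apply to the raw count. The article does not say how counts convert to item points, so the attenuation of the 0–9 score cannot be computed from it.

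**The case against.** The strongest reply is that this is only a caveat on interpretation. FROP-Com is secondary and drives neither the sample size nor the falls-rate comparison. Two of its three items carry no stated 12-month look-back. The PPA, an objective set of five physiological subtests with no falls-history item, covers the same construct, and TUGT, gait speed, chair stands and FES-I cover related factors. All of that stands and limits the weight of the point.

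Four stronger readings are tempting, and the documents do not support them:
- **The item cannot respond to treatment.** It can: a quarter of its window is on-study at the first follow-up and three quarters at the last.
- **The comparison between groups is biased.** Falls before baseline precede randomisation and are balanced in expectation. The effect is lost sensitivity.
- **Falls are counted a second time by recall.** The article does not say whether the item is scored from memory or from the diary at follow-up. The diary could serve for the on-study months, but it cannot cover the months before baseline, so the window problem remains either way.
- **FROP-Com is offered as independent confirmation of the falls rate.** No such claim is made. The overlap at 9 months concerns one item of three and matters only if a reader treats the two results as separate evidence.

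It is also fair to object to replacing the published total with an ad hoc two-item sum. Under Participants, eligibility admits only people with little or no IADL difficulty, so that item probably starts near its floor. A two-item sum may then rest mostly on balance, which TUGT already measures. This is a reason to report the items alongside the total, not in its place.

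**Conclusion.** The point holds as one of attenuation and partial duplication. The measurement rule as written makes the falls item of FROP-Com, and any high/low-risk class built on it, insensitive mainly at the post-intervention comparison, where about 75–77% of the window precedes the intervention. At the last visit the share is about 25–27%, and the rest overlaps the falls already counted as the primary outcome.

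The shares rest on the nominal 12 weeks and 6 months; the actual dates move them within the bounds shown. The 10% and 30% rest on a constant rate and an assumed 40% effect from day one.

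A reader might infer that the trial's fall-risk aim is undermined. It is not, because the PPA does not depend on this item. The point is minor to moderate and confined to one secondary outcome.

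**What to change.** Before the analysis, state how FROP-Com is handled at each visit:

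1. Keep the full score at baseline, and use it as a covariate.
2. At both follow-up visits, pre-specify analysis of the IADL and balance items, separately or summed, alongside the published total.
3. Take on-study falls from the prospective diary.
4. Do not interpret the post-intervention total, or its 0–3/4–9 class, as a treatment effect on fall risk without stating the overlap with the pre-intervention period. At the last visit, note the overlap with the primary outcome.
5. Rest the overall fall-risk conclusion mainly on the PPA.

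The cost is analysis wording; no new data are needed. The downside is small: the item-level result is not the published score, has no cut-off, and may reflect mostly balance because eligibility limits IADL impairment.
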